### Analysis and sample size

The comparison between pre-and post-feedback functional outcomes will be done by using generalized linear model that treats the intervention as an effect that is either present or absent for a patient (absent for the pre-feedback cohort and present the post-feedback cohort). In the analysis the surgeons will be considered as clusters to account for repeated measurements. In the model other covariates like patient age, tumour stage, tumour grade, pre-operative PSA, baseline urinary function, baseline sexual function, and nerve preservation status will be used. An estimate of the difference between pre-feedback and post-feedback potency or continence will be obtained from the above model.

An overall improvement of 10% in potency or incontinence following the surgeon feedback intervention (post-intervention cohort) will be considered clinically significant. Assuming a baseline potency of 20% and a baseline continence of 70%, 294 patients would be required for 80% power at an alpha of 5%. Assuming as much as a 30% lost to follow up, we will require a minimum of 210 patients in the pre-feedback cohort and 210 patients in the post-feedback cohort.

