In a 2006 provincial pathology audit, positive surgical margins were found in 33% of patients who had tumours that did not extent outside the prostate (pathologic stage T2) in Ontario, Canada (population 12,160,282). In 2008, a Cancer Care Ontario expert clinician panel set a provincial goal to reduce the incidence of positive surgical margins to less than 25% [22]. Since that time, Cancer Care Ontario has been providing feedback to clinicians on the incidence of positive surgical margins in their patients. As of 2011, the incidence of pT2 positive surgical margins in Ontario had dropped to 21% [23]. This finding supported the hypothesis that prospective reporting and feedback can affect surgeon behaviour, resulting in improvement. The findings in Ontario are consistent with randomized trials that show feedback to clinicians generally result in practice improvement [24].

A potential negative consequence of surgical margin scrutiny by Cancer Care Ontario is that surgeons may be performing a wider excision of peri-prostatic tissue, purposely sacrificing erectile nerve tissue to lower the risk of a positive margin, and as a result compromise urinary and sexual function. Clearly, a balance must be struck between ensuring complete cancer removal and preservation of a patient’s urinary and sexual function. Isolated critical evaluation of surgical margin rates may have had the unintended effect of increasing long term side effects that are important to patients. Ideally, all clinically important outcomes should be assessed when evaluating surgical quality, not only surgical margin status.

The primary purpose of this study is to determine if providing prostate cancer surgeon feedback on their patients’ improves overall surgical quality as measured by surgical margin rates and patient reported functional outcomes.

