### Study participants

All prostate cancer surgeons will participate in this study. While all surgeons will use a common clinical pathway and provide consistent information, the surgical technique is not mandated by the study. All patients undergoing radical prostatectomy by each surgeon will be eligible, regardless of tumour stage, histology and previous pelvic treatments including surgery or radiation. Extent of planned and performed neurovascular bundle preservation will not be mandated, but will be prospectively collected from the operating surgeon. Surgeons will report their nerve spare intent prior to surgery and their perceived nerve spare achieved following surgery. All surgical approaches (open, laparoscopic, and robotic assisted laparoscopic) will be included. Given that patients are contacted for assessment of symptoms, consent will be obtained from each patient. Patients will be excluded if they 1) decline or are incapable of providing consent; 2) are less than 18 years of age; or 3) are being treated outside of The Ottawa Hospital. Patient information and outcomes will be collected prior to surgery and 6- and 12-months following surgery. Approximately 230 radical prostatectomy procedures are performed annually at The Ottawa Hospital.

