### Surgical report card intervention and control

Descriptive baseline, pathological, and follow-up information will be summarized and tabulated. The primary measures of surgical quality on the surgeon report cards will be: post-operative urinary continence, post-operative erectile function (stratified by baseline function and tumour stage), and rate of positive surgical margins (stratified by tumour stage). An example of a surgical report card is displayed in Additional file 1. Urinary continence will be defined as requiring no continence pads (i.e. score of 0 on question 5 of the EPIC questionnaire), and potency will be defined as a firm enough erection for intercourse (score of 4 on question 18 of the EPIC questionnaire). Changes in patients’ overall health status will also be summarized.

For the pre-feedback cohort, pre-operative, 6-month, and 12-month patient data will be collected but there will be no report cards distributed to surgeons. This will form the pre-feedback cohort. When accrual to the pre-feedback cohort is complete (anticipated to be 12 months from initiation of the study), surgeons will begin receiving report cards. Patients treated after the provision of report cards will form the post-feedback cohort for analyses. A summary of the study timeline is presented in Fig. 1.

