### Outcomes

The primary outcomes will be post-operative function of the patient cohort before surgeon feedback (pre-feedback cohort) compared to post-operative function of the patient cohort after surgeon feedback (post-feedback cohort). The secondary comparison will be the proportion of patients with positive surgical margins in the pre-feedback cohort compared to post-feedback cohort. Outcomes will be stratified or adjusted by important co-variates such as patient age, tumour stage, tumour grade, pre-operative PSA, baseline urinary function, baseline sexual function, and nerve preservation status.

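### The primary model adjusts for nerve preservation, a surgeon's choice made after report cards begin, so its estimate leaves out any feedback effect that acts through nerve sparing

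*Protocol article*

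**What the plan says.** The Analysis and sample size section compares functional outcomes between cohorts with a generalized linear model. Its covariates are age, tumour stage and grade, PSA, and then "baseline urinary function, baseline sexual function, and nerve preservation status will be used". The primary result comes from that model: "An estimate of the difference between pre-feedback and post-feedback potency or continence will be obtained from the above model". The improvement regarded as clinically significant, 10% in potency or continence, is described as an overall one.

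The Outcomes section names the same variable. "Outcomes will be stratified or adjusted by important co-variates", and the examples end with "baseline urinary function, baseline sexual function, and nerve preservation status". That sentence follows both the functional and the surgical-margin comparisons, so it covers margins too.

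Three other statements fix what kind of variable this is:

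- Study participants: "Extent of planned and performed neurovascular bundle preservation will not be mandated".
- Study participants, on recording: "Surgeons will report their nerve spare intent prior to surgery and their perceived nerve spare achieved following surgery".
- Surgical report card intervention and control: "Patients treated after the provision of report cards will form the post-feedback cohort for analyses".

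The Background describes what surgeons may have done under earlier provincial feedback on margins: "purposely sacrificing erectile nerve tissue to lower the risk of a positive margin, and as a result compromise urinary and sexual function".

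**The concern.** A covariate used to make two cohorts comparable should be one that the intervention cannot change. Nerve preservation does not meet that test here. It is left to the surgeon, and in the post-feedback cohort the surgeon makes the choice after report cards have begun. The protocol does not say whether intended or achieved sparing enters the model, but both come after the intervention.

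The Background also gives a concrete reason to expect feedback to change it, and to expect function to change as a result. Adjusting for it compares patients at the same sparing status and sets aside any change in how often nerves are spared. The study asks whether feedback improves results overall, and a change in sparing is one way it could.

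Two errors become possible. If report cards lead to more sparing and better function, the estimate is too small. If they lead to less sparing and worse function, the adjusted estimate hides the loss. That second case is the unintended harm the Background worries about.

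There is a further, smaller risk. Conditioning on a choice made after the intervention can bring in bias from unmeasured reasons for that choice, so the adjusted figure is not guaranteed to be a clean direct effect either.

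**Working it through.** **Order of events (protocol article).** Report cards start; the surgeon forms and records an intent to spare; the operation takes place; perceived sparing is recorded; function is measured at 6 and 12 months. Nerve preservation lies between intervention and outcome. Age, PSA, clinical stage and baseline function do not.

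**Inputs from the plan.** Baseline potency is 20% and the target gain is 10%, read here as percentage points (20% to 30%). The plan's own sample-size figure supports that reading. The two-proportion formula with two-sided 5% and 80% power gives

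n = [1.96·√(2·0.25·0.75) + 0.842·√(0.2·0.8 + 0.3·0.7)]² / 0.10² ≈ 293.2, rounded up to 294 per cohort.

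The plan quotes 294, though it uses it as the total for both cohorts. That is a separate matter, and no sample size enters the rest of this check.

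**Assumed inputs (not in the documents).** Potency is 40% with and 5% without sparing. A share s of the 10-point gain comes through more sparing, and the rest is a direct gain equal in both sparing groups. There is no unmeasured confounding of sparing and function.

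**Formulas.**

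- Baseline sparing rate: m0 = (0.20 − 0.05)/(0.40 − 0.05) = 0.15/0.35 = 42.9%. Check: 0.429·0.40 + 0.571·0.05 = 0.20.
- Post-feedback sparing rate: m1 = m0 + s·0.10/0.35.
- Total effect: s·0.10 + (1 − s)·0.10 = 10 points for every s.
- Effect within sparing strata, which the adjusted model estimates: (1 − s)·10 points.

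The simulated columns are risk differences from models fitted to 400,000 simulated patients, without and with the nerve covariate.

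| Share through sparing | Sparing after feedback | Without covariate, simulated | With covariate, exact | With covariate, simulated |
|---|---|---|---|---|
| 0% | 42.9% | 10.2 | 10.0 | 10.1 |
| 25% | 50.0% | 10.0 | 7.5 | 7.6 |
| 50% | 57.1% | 9.9 | 5.0 | 5.0 |
| 75% | 64.3% | 9.9 | 2.5 | 2.4 |
| 100% | 71.4% | 10.0 | 0 | 0.0 |

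Small departures from the exact values are simulation error. The 40% and 5% only set how far sparing must move; the adjusted result depends on s alone. I compare risk differences because an odds ratio moves when a strong covariate is added even with no mediation (1.73 without and 1.91 with, at s = 0).

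**Opposite direction, same assumed rates.** Suppose sparing falls by 0.05/0.35 = 14.3 points, from 42.9% to 28.6%, with no direct effect. Potency becomes 0.286·0.40 + 0.714·0.05 = 15.0%, a loss of 5 points. The adjusted model shows 0.

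**Continence.** The documents give nothing from which to set a mediated share, so no figure is offered.

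**The case against.** The best defence is case mix. This is a non-randomised before-and-after study that takes all stages and patients with earlier pelvic treatment. Whether nerves can be spared depends partly on where and how extensive the tumour is, and age, stage, grade and PSA may not capture all of that. Dropping the covariate could leave some residual confounding. This stands as a small cost of the fix. It does not make the adjusted figure an overall effect. The main case-mix variables are already in the model, and the report card itself stratifies erectile function by baseline function and stage, not by nerve preservation.

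A second defence is latitude. Both covariate lists are worded as examples, the abstract allows adjustment as appropriate, and a fuller plan may contain other analyses. But the Analysis section names this covariate, says it will be used, and takes the primary estimate from that model.

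A reader might also infer more than the text supports:

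- *That nerve sparing is the main route by which report cards act.* The Background passage describes a possible harm of a different, margin-only feedback programme. Elsewhere the Background ties function to surgical technique in general, which leaves room for better dissection at the same recorded sparing status.
- *That adjustment removes the whole effect.* This is true only if all of it is mediated.
- *That the Analysis section fixes a nerve-adjusted margin model.* It specifies a model for functional outcomes only. Margins are reached through the Outcomes section.
- *That stage and grade are post-intervention too.* Both clinical and pathological values are collected, and the model description does not say which is used. That is an open question and not an error shown by the text.

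**Conclusion.** The point holds in a limited form. The model that supplies the primary estimate conditions on a variable the intervention can change and that the protocol's own rationale links to function. The result would be the effect not passing through nerve preservation, while the target is an overall gain.

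The existence of the problem follows from the text. Its size does not. For a true 10-point potency gain the adjusted estimate can lie anywhere from about 10 points (no mediation) to about 0 (full mediation), on the assumptions of a constant direct effect and no unmeasured confounding of sparing and function. The bias can run either way: a benefit understated if sparing rises, harm masked if it falls. It matters enough to correct before the cohorts are compared, because it decides what the primary result means.

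**What to change.** 1. In Analysis and sample size, remove nerve preservation status from the primary functional model.
2. In Outcomes, remove it from the covariates for the margin comparison as well.
3. Adjust for the pre-operative variables already collected: age, clinical stage, pre-operative grade, PSA and baseline EPIC function. Say explicitly that stage and grade are the pre-operative values.
4. Report intended and achieved nerve sparing by cohort as a process outcome, so that a shift in either direction is visible.
5. Keep the nerve-adjusted model as a secondary analysis labelled as mediation, with its assumptions stated.

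The cost is a short change to two covariate lists and one added table; no new data are needed. The downside is that nerve status may hold some case-mix information that the pre-operative variables miss. The secondary model can be used to examine this, read alongside the sparing rates by cohort.

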**Methods:**

We propose a prospective cohort quasi-experimental study. The intervention is the provision of feedback to prostate cancer surgeons via surgical report cards. These report cards will be distributed every 3 months by email and will present surgeons with detailed information, including urinary function, erectile function, and surgical margin outcomes of their patients compared to patients treated by other de-identified surgeons in the study. For the first 12 months of the study, pre-operative, 6-month, and 12-month patient data will be collected but there will be no report cards distributed to surgeons. This will form the pre-feedback cohort. After the pre-feedback cohort has completed accrual, surgeons will receive quarterly report cards. Patients treated after the provision of report cards will comprise the post-feedback cohort. The primary comparison will be post-operative function of the pre-feedback cohort vs. post-feedback cohort. The secondary comparison will be the proportion of patients with positive surgical margins in the two cohorts. Outcomes will be stratified or case-mix adjusted, as appropriate. Assuming a baseline potency of 20% and a baseline continence of 70%, 292 patients will be required for 80% power at an alpha of 5% to detect a 10% improvement in functional outcomes. Assuming 30% of patients may be lost to follow-up, a minimum sample size of 210 patients is required in the pre-feedback cohort and 210 patients in the post-feedback cohort.

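### The 294 (abstract: 292) patients needed for 80% power is a per-cohort number but is used as the total for both cohorts, so 210 per cohort gives about 51% power

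*Protocol article*

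**What the plan says.** The section *Analysis and sample size* of the protocol article gives every input of a two-proportion calculation:

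- Baseline rates: "Assuming a baseline potency of 20% and a baseline continence of 70" percent.
- Target effect: "An overall improvement of 10% in potency or incontinence following the surgeon feedback intervention" is named as clinically significant.
- Requirement: "294 patients would be required for 80% power at an alpha of 5" percent.
- Attrition allowance: 30%, as an upper bound.
- Enrolment that follows from it: "we will require a minimum of 210 patients in the pre-feedback cohort and 210 patients in the post-feedback cohort".

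The abstract gives a slightly different requirement, "292 patients will be required for 80% power at an alpha of 5% to detect a 10% improvement in functional outcomes", and the same 210 per cohort. Neither place says whether 294 or 292 is per cohort or in total. It is also not stated whether alpha is one- or two-sided, or whether the 10% is absolute or relative.

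The comparison is between two separate groups of patients. The same section describes the intervention as "absent for the pre-feedback cohort and present the post-feedback cohort".

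**The concern.** Detecting a move from 20% to 30% between two independent groups with 80% power usually takes nearly 300 patients in each group. A plan that reaches 80% with 294 patients across both groups, before any allowance for clustering by surgeon, looks as if a per-group result was taken for a total.

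Post-operative function is the primary outcome. If the power is well below 80%, a real gain of the size the authors call clinically significant could easily fail to reach significance. A reader told that the study had 80% power could then take such a result as evidence that report cards do not help. The discussion also offers the design for use in other hospitals and regions, so the sample-size figure could be copied.

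**Working it through.** **Inputs.** All are from *Analysis and sample size*: p1 = 0.20 and p2 = 0.30 for potency; p1 = 0.70 and p2 = 0.80 for continence; power 80% (z = 0.8416); alpha 5% (z = 1.96 if two-sided); loss 30%; 210 enrolled per cohort. Two-sided testing and an absolute 10-point effect are assumptions. They are the readings that reproduce the published figure.

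**Step 1: reproduce 294.** With pooled variance under the null and no continuity correction,

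n per cohort = [z(α/2)·√(2·p̄·(1−p̄)) + z(β)·√(p1(1−p1) + p2(1−p2))]² / (p2−p1)²

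For potency, p̄ = 0.25:

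n = [1.96·√0.375 + 0.8416·√(0.16 + 0.21)]² / 0.10² = (1.2003 + 0.5119)² / 0.01 = 293.15, rounded up to **294 per cohort**.

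Continence has p̄ = 0.75 and the same variances (0.21 + 0.16), so the result is identical. The arcsine formula gives 291.7, rounded up to 292 per cohort, which matches the abstract.

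**Step 2: see how the plan used it.**

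- 294 / 0.70 = 420 = 210 + 210.
- Equivalently, 210 × 0.70 = 147 evaluable per cohort, and 2 × 147 = 294.

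So 294 was inflated for loss and then split across the two cohorts. Used as a per-cohort number, it would give 294 / 0.70 = 420 enrolled in each cohort.

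**Step 3: power of the plan as written.**

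Power = Φ{[0.10 − z·√(0.375/n)] / √(0.37/n)}

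At n = 147, two-sided: Φ[(0.10 − 0.0990) / 0.0502] = Φ(0.020) = **0.508**.

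| Evaluable per cohort | Two-sided 5% | One-sided 5% |
|---|---|---|
| 147 (210 less 30%) | 50.8% | 63.2% |
| 210 (no loss) | 65.9% | 76.6% |
| 294 | 80.1% | 87.8% |

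The figures are the same for potency and continence.

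**Step 4: difference detectable with 80% power at 147 per cohort, two-sided.** Solving the Step 1 formula for p2 gives about 14.5 points for potency (20% to 34.5%) and about 13.7 points for continence (70% to 83.7%).

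**Step 5: look for a reading in which 294 is a valid total.**

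- One-sided alpha: 229 to 231 per cohort depending on the variance formula, so at least 458 in total.
- Two-sided with continuity correction: 313 per cohort.
- A relative 10% improvement: 623 per cohort for continence (70% to 77%) and 6,510 for potency (20% to 22%).
- One sample against a fixed rate, two-sided: about 137 (potency) or 153 (continence). That is neither 294 nor the planned design.

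None of these gives a two-cohort total of 292 to 294.

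**The case against.** - **The label is inferred.** The article never says that 294 is a total. That is true, but 420 × 0.70 is exactly 294. If 294 were meant per cohort, 210 per cohort would fall short even before any loss.
- **51% is the pessimistic end.** The 30% loss is worded as an upper bound and 210 as a minimum. This stands as a qualification: the two-sided range is about 51% (full loss) to 66% (no loss). Even with no loss and one-sided testing, 210 per cohort reaches only 76.6%.
- **The planned analysis is not this simple test.** It is a generalized linear model with baseline covariates and surgeons as clusters. Adjustment may raise power, and clustering may move it either way. The document gives no figures for either and does not use them to support 294. For 147 patients to do the work of 294, the variance of the effect estimate would have to be halved (147/294 = 0.5), which the article does not claim.
- **Success might mean either endpoint.** If both effects were real, the endpoints independent and no multiplicity correction made, the chance of at least one significant result would be 1 − (1 − 0.508)² = 76% two-sided, or about 86% one-sided. The article does not invoke this reading, independence is an assumption, and 294 is the single-endpoint number. The objection does limit the statement that an effect is missed about half the time to each endpoint taken separately.
- **292 versus 294 is editorial.** This is right. The abstract's figure gives 292 / 2 / 0.70 = 208.6, so practically the same cohort size, and nothing in the conclusion depends on it.

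**Conclusion.** The concern holds: the sample size, power and effect stated in the article cannot all be true. A per-cohort requirement was used as the total for both cohorts, which halves the information the calculation asks for. After the planned 30% loss, each endpoint has 50.8% power for a 10-point gain instead of 80%, an overstatement of about 29 percentage points. With no loss the power is 65.9%. No combination of sidedness and loss brings a single endpoint to 80% with 210 per cohort.

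The power figures rest on an absolute 10-point effect and an unadjusted comparison without clustering, and the main figure on two-sided 5% testing. These are the assumptions that reproduce the article's own number. Covariate adjustment and clustering could shift the true power by an amount the document does not allow one to calculate.

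**What to change.** Correct the sample-size paragraph and the abstract together:

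1. State that 294 evaluable patients are needed in each cohort, say that the calculation is two-sided with an absolute 10-point difference (if that was the intention), and use one figure in both places.
2. Replace the 80% claim with what 210 enrolled (147 evaluable) per cohort delivers: about 51% power per endpoint for 10 points, rising to 66% with no loss; or 80% power for about 14.5 points in potency and 13.7 in continence.
3. Add that a non-significant result will not exclude a 10-point effect and will be read through the 95% confidence interval.

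The cost is a rewording and a less favourable power statement. No extra patients are needed. Restoring 80% power for 10 points on the plan's own assumptions would take 420 enrolled per cohort. The article says "Approximately 230 radical prostatectomy procedures are performed annually at The Ottawa Hospital", so that would need at least 420 / 230 = 1.8 years per cohort, even if every patient took part, against an anticipated 12 months for the pre-feedback cohort. Restating the power is therefore the proportionate correction.
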